### Eligibility criteria

2.3

#### Diagnostic criteria

2.3.1

1.The diagnostic criteria of Western medicine refer to the Rome IV consensus on diagnosis and treatment of functional gastrointestinal diseases.^[18]^2.The TCM diagnostic criteria of the liver depression and spleen deficiency syndrome refer to consensus of TCM experts in diagnosis and treatment of Irritable Bowel Syndrome in 2017.^[19]^ TCM syndrome differentiation including the primary and secondary symptoms as following:Primary symptoms:(1)abdominal pain accompanied by diarrhea and(2)prone to irascible or irritable.Secondary symptoms:(1)distending pain in hypochondrium,(2)reduced appetite, and(3)presented with fatigue.Auxiliary symptoms: light and enlarged tongue or tooth-marked tongue with white greasy coating, string pulse.

#### Inclusion criteria

2.3.2

(1)Diagnosed with IBS-D.(2)Agree to have a colonoscopy or provide a colonoscopy report within 3 months.(3)The score of IBS-SSS scale was more than 75.(4)TCM syndrome differentiation belonged to liver depression and spleen deficiency syndrome(5)Age >18 and < 65 years.(6)Voluntary to participate and providing written informed consents.

#### Exclusion criteria

2.3.3

(1)Patients with organic diseases and history of abdominal surgery.(2)Patients with contraindications for enteroscopy.(3)Patients with severe diseases of major organs such as liver, brain, kidney, and mental disorders.(4)Patients with systemic diseases affecting gastrointestinal motility (such as hyperthyroidism, diabetes, chronic renal insufficiency, etc).(5)Patients are currently pregnant and lactating.(6)Patients who had used other drugs for the treatment of irritable bowel syndrome within one week before screening.(7)Patients with allergic constitution or have an allergy to trial medication.(8)Patients have a history of alcohol or drug abuse.(9)Patients have participated in other clinical trials within three months.

#### Termination and withdrawal criteria

2.3.4

(1)The patients are unwilling to continue the clinical trial.(2)No medication or any follow-up.(3)Poor compliance.(4)Serious adverse events occurred in the course of the study.(5)The treatment plan caused obvious discomfort to the patients in the course of treatment.

### Randomization and blindness

2.4

Institute of Clinical Pharmacology of Xiyuan Hospital, China Academy of Chinese Medical Sciences was responsible for generating the allocation sequence. Random allocation method: using SAS 9.4 (SAS Institute Inc., Cary, NC) to generate random sequences, randomly grouping, and coding drugs; Concealment and implementation of allocation scheme: the secret envelope method was used to conceal the random sequences.

The double-blind trial blinded the implementers of the study (doctors) and the subjects (patients). In order to avoid the impact of blindness on other research subjects due to serious adverse conditions, only a number is given to each study object, and the medicine is distributed according to the number. Doctors and patients can only have access to the blind number in this process, and the blind bottom is kept by a person who will not participate in this study. In the event of an emergency or when the patient needs to be rescued, it is necessary to know what kind of treatment the patient is receiving, the corresponding emergency letter shall be opened in the presence of at least two researchers, and the emergency letter shall be collected together with the case report form after the end of the trial. Blind bottom leakage or emergency letter reading should not exceed 20% before the end of the trial.

### Research person

2.5

Experienced physicians, as investigators, will take direct charge of recruiting and evaluating participants in this trial. Postgraduates in gastroenterology will be responsible for dispatching drugs, filling in case report forms, and recording detailed reasons for the participants’ withdrawal from the trial. And they will be trained by the principal investigator before participating in this trial.

### Recruitment and encouragement

2.6

A total 72 patients will be recruited from the gastroenterology department clinic or ward at Dongfang Hospital, Beijing University of Chinese Medicine, from January 2020 until December 2022. Before the recruitment, all the participants will be fully informed about consent of this trial, including therapeutic interventions, trial benefits, and possible risks. Participants could be enrolled in it only after signing their written informed consent. Meanwhile, in order to guarantee the completeness of this trial, we will handsel drugs to the patients who participate it completely.

### Collection of biological specimens

2.7

The participants’ blood, stool and urine samples will be collected before and after intervention, and clearly marked in a uniform format. A designated investigator will isolate T lymphocytes single cells from the blood samples in the laboratory. Then, the isolated single cells were put into 3.5 μ l lysate and repeatedly blown with a pipette for several times, and then immediately stored at -80°C, finally transported to Shanghai OE Biotech Co., Ltd (Shanghai, China) for transcriptome sequencing.

## Intervention

3

### Medications

3.1

TXACD (TXACD granules supplied by Beijing Tcmages Pharmaceutical Co., LTD, Beijing, China), pinaverium bromide tablets (PBT, 50 mg/tablet, supplied by Beijing Wansheng Pharmaceutical Co. LTD, Beijing, China), and placebos are prepared respectively in accordance with the 2 above drugs in terms of appearance, smell, taste, packaging, label and other characteristics (TXACD granule placebo is supplied by Beijing Tcmages Pharmaceutical Co., LTD, Beijing, China; PBT placebo is supplied by Beijing Wansheng Pharmaceutical Co. LTD, Beijing, China). TXACD is composed of seven Chinese herbs, including Baizhu (Atractylodes Macrocephala Koidz), Baishao (Paeoniae Radix Alba), Huanglian (Coptidis Rhizoma), Paojiang (Rhizoma Zingiberis Preparata), Chenpi (Citrus Reticulata), Chantui (Cicadae Periostracum), Wumei (Mume Fructus). In this trial, an administrator is assigned to manage the drugs, including drug storage, distribution, and recycling and record the detailed information timely.

### Intervention schedule

3.2

TXACD granule or placebo will be orally administered one packet after dissolved twice a day (1 h after the meal) for 4 weeks. Pinaverium bromide tablets or placebo will be administered one tablet three times a day (swallowed with meals). During the study, participants will be asked to stop taking the medications associated with IBS-D. Probiotics, functional foods and dietary supplements are also banned. Participants will be obligated to fill out daily study diaries, including medication administration records, accompanying treatments, and dietary questionnaires to help check compliance and statistically correct dietary bias. The presence of worsening IBS-D symptoms, which require recording in the Case Report Form (CRF), allows rescue medication to be used for less than 1 week.

### Follow-up

3.3

Each participant will have a participant diary card recording signs and symptoms of abdominal pain and fecal character. After enrolling in the trial, participants will be interviewed every two weeks, and they should return any remaining medication and packaging, and receive medications they need to take for the next two weeks. The evaluation of study endpoints and follow-up duration is shown in Figure 2.

### Outcome measurements

3.4

#### Primary outcome

3.4.1

The primary outcome of our trial is the response rate to the IBS Symptom Severity Score (IBS-SSS).^[20]^ Respondents were defined as having 50% or more reduction in IBS symptoms compared to baseline. IBS-SSS will be evaluated at baseline, week 2, week 4 and week 8.

#### Secondary outcome

3.4.2

The secondary outcomes including TCM syndrome score, adequate relief (AR) and IBS-Quality of Life Questionnaire (IBS-QOL).

#### TCM syndrome score

3.4.3

According to the diagnostic criteria of liver depression and spleen deficiency syndrome, the main symptoms, secondary symptoms will be graded and scored. All the indexes will be recorded at baseline, week 2, week 4 and week 8.

According to the referred Guidance Principle of Clinical Study on New Drug of Traditional Chinese Medicine,^[21]^ All the symptoms will be divided into four grades: none, mild, moderate and severe, with 0, 2, 4 and 6 points in the main symptoms; 0, 1, 2 and 3 points in the secondary symptoms. The tongue and pulse manifestations will be divided into normal and abnormal grades, 0 and 2 points in the main symptoms, and 0 and 1 points in the secondary symptoms.

The clinical efficacy is evaluated as follows:

(1)Clinical recovery: clinical symptoms disappeared or syndrome score decreased by ≥95% from the baseline.(2)Marked efficacy: the syndrome score decreased by ≥70% and <95% compared with the baseline.(3)Efficacy: the syndrome score was a decrease of at least 30% and less than 70% from the baseline.(4)Invalid: the syndrome score was a decrease of less than 30% from the baseline.(5)Worsen: the syndrome score exceeded the baseline after treatment.(6)TCM syndrome efficacy rate = (Clinical recovery + Marked efficacy + Efficacy) cases /a total number of cases × 100%.

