#### Clinical data analysis

3.7.1

Data analysis will be performed by professional statisticians and principal investigator using IBM SPSS Statistics (Version 24.0 position IBM Corp., Armonk, NY). Statistical analysis included actual number of subjects selected, cases of detachment and rejection, demographic and other baseline characteristics, patient compliance, efficacy, and safety analysis. Categorical variables will be described by frequency tables or percentages and continuous variables will be described by mean ± standard deviation. Categorical data will be analyzed by chi-square test or Fisher exact test to compare the differences between the two groups. Besides, quantitative data with normal distribution will be analyzed by T test. If the data does not conform to normal distribution or variance uniformity, Wilcoxon rank sum test or Wilcoxon signed test will be used for comparison between the two groups. A 2-sided *P* < .05 indicates statistical significance. For missing data, sensitivity analysis will be conducted and the optimal approach to the imputation of missing data will be proposed.

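### The graded TCM efficacy evaluation loses power under a consistent shift across grades, because both the 30% cut and the chi-square/Fisher rule ignore the order of the five levels

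*Protocol article*

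**What the plan says.** Section 3.4.2 lists the secondary outcomes: "The secondary outcomes including TCM syndrome score, adequate relief (AR) and IBS-Quality of Life Questionnaire (IBS-QOL").

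Section 3.4.3 builds a numeric TCM score, recorded at baseline and weeks 2, 4 and 8. It then evaluates clinical efficacy by sorting the percentage change into five levels. The top level is "Clinical recovery: clinical symptoms disappeared or syndrome score decreased by ≥95% from the baseline". Marked efficacy comes next (a fall of 70% to under 95%), followed by "Efficacy: the syndrome score was a decrease of at least 30% and less than 70% from the baseline". Below that are an invalid level (a fall under 30%) and "Worsen: the syndrome score exceeded the baseline after treatment". One summary is defined from these levels: "TCM syndrome efficacy rate = (Clinical recovery + Marked efficacy + Efficacy) cases" divided by the total number of cases. This is a cut at a 30% fall.

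Section 3.7.1 gives one rule for categorical variables: "Categorical data will be analyzed by chi-square test or Fisher exact test to compare the differences between the two groups". Separately, "quantitative data with normal distribution will be analyzed by T test", and "If the data does not conform to normal distribution or variance uniformity, Wilcoxon rank sum test or Wilcoxon signed test will be used" for the comparison of the two groups. No ordinal method is named for categorical data.

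**The concern.** The five levels run in a clear order from worse to recovered, but neither categorical route uses it.

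- **The pooled rate.** A 31% fall counts the same as full recovery, and a 29% fall counts the same as deterioration.
- **The five grades under the general categorical rule.** A Pearson chi-square on a 2x5 table gives the same P value if the columns are shuffled. It spends 4 degrees of freedom on departures of any shape.

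If TXACD moves patients up the scale at every level, both routes are less sensitive than a test that uses order. With only 30 to 36 patients per arm, a null result on the graded evaluation could easily reflect the choice of test. The issue is efficiency: chi-square and Fisher remain valid tests of the hypotheses they address.

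**Working it through.** **Inputs from the article.** Section 2.2 gives 1:1 allocation and 30 per arm (60 in total), raised for 20% dropout to 72. The stated total is reproduced by 60 × 1.20 = 72, which is 36 per arm. Section 3.7.1 gives two-sided P < .05. No power, effect size or grade distribution is given for the TCM outcome, so the plan has no power figure to reproduce.

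**Assumed inputs.** Three control-arm distributions were used, from worst to best grade in percent: A (5, 25, 45, 20, 5), B (5, 35, 40, 15, 5) and C (3, 17, 45, 30, 5). The treated arm follows a proportional-odds shift: at every cut, odds(treated) = OR × odds(control), with OR 2.5 or 3.

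**What the shift means at the 30% cut.** For A, the control rate is 45 + 20 + 5 = 70%, odds 0.70/0.30 = 2.33. With OR 3 the odds are 7.0 and the treated rate is 7/8 = 87.5%. For B, 60% becomes 4.5/5.5 = 81.8%. For C, 80% becomes 12/13 = 92.3%.

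**Power by simulation** (10,000 trials per row; asymptotic tests; rank sum corrected for ties):

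| Control | OR | n per arm | Rank sum, 5 grades | 2x5 chi-square | Rate, 2x2 chi-square | Loss, 2x5 | Loss, rate |
|---|---|---|---|---|---|---|---|
| A | 2.5 | 30 | 47% | 25% | 29% | 22 | 18 |
| A | 3 | 36 | 70% | 45% | 44% | 25 | 26 |
| B | 2.5 | 30 | 48% | 25% | 35% | 22 | 12 |
| B | 3 | 36 | 71% | 46% | 55% | 25 | 16 |
| C | 2.5 | 30 | 46% | 26% | 23% | 21 | 24 |
| C | 3 | 36 | 71% | 47% | 35% | 24 | 35 |

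Losses are in percentage points, taken from unrounded powers. With OR 1 the rank sum test rejected in about 5% of trials, so the gain does not come from an inflated type I error.

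**Wider assumptions, still a shift in one direction.** The scenarios were OR 2 to 4 with control response rates of 45% to 87%, and normally distributed percentage falls shifted by 0.5 to 0.8 SD. The loss against rank sum is about 14 to 25 points for the 2x5 table and 5 to 54 for the rate by chi-square. For the rate by Fisher, which section 3.7.1 also permits, it is 12 to 74. For example, with OR 3, a control rate of 65% and 36 per arm, rank sum has 71%, the rate by chi-square 50% and the rate by Fisher 40%.

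**Effect concentrated at the 30% cut.** Take control A against treated (1, 4, 70, 20, 5), with 36 per arm. Only the boundary between the invalid and efficacy levels is crossed in any number, and the top two grades are unchanged. Rank sum then has 34% power, the 2x5 chi-square 66% and the rate 85%. Another pattern of this kind gave 42%, 69% and 82%. The order of the tests is reversed.

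**The uncoarsened measure.** With normal percentage falls, a 0.67 SD shift and 36 per arm:

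- Control mean 60%, SD 25: t test 79%, rank sum on grades 73%, 2x5 chi-square 51%, rate 30%.
- Control mean 30%, SD 30: t test 80%, rank sum on grades 74%, 2x5 chi-square 49%, rate 60%.

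In these settings the ungraded measure does at least as well as the best analysis of the grades.

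**The case against.** The strongest reply is that the named secondary outcome is the numeric score, which section 3.7.1 already sends to the t test or the Wilcoxon test. A full-information comparison is therefore available under the plan as written, and the rate may be only an accompanying responder summary of a familiar kind. This stands, and it limits the point. A reader might infer that the whole TCM secondary outcome is underpowered, but the documents do not support that. What remains is that section 3.4.3 evaluates clinical efficacy only through the grades and the rate, and the article does not say whether score or rate is the comparison between arms.

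A reader might also infer that the plan specifies a 2x5 chi-square on the grades. It does not. That test follows only from applying the general categorical rule to them, and for the two-level rate chi-square or Fisher is a proper test.

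A third objection is that a proportional-odds shift favours rank methods. That is fair, and the reversal at the 30% cut shows that no single loss figure is a property of this plan.

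Finally, an unseen analysis plan may settle which test applies. It may, but the article itself states a test rule for categorical data, and that rule ignores order.

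**Conclusion.** The point holds for the graded and rate evaluation. Five ordered levels are defined, the only summary taken from them is a 30% cut, and the only categorical tests named ignore order. For a consistent shift with OR 2.5 to 3 and 30 to 36 per arm, the loss is roughly 20 to 25 points against a 2x5 chi-square and roughly 10 to 36 against the rate. Both figures rest on assumed control distributions and assumed effects. The wider range for the rate by chi-square is about 5 to 54 points, and the rate does better than rank sum when the benefit sits at the 30% threshold. The numeric score is untouched, and so is the primary outcome. The practical impact is modest, but the change is worth making because it is nearly free.

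**What to change.** In section 3.7.1:

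1. State that the TCM comparison between arms is made on the numeric syndrome score, by the tests already given for quantitative data.
2. State that where the five grades are compared, the Wilcoxon rank sum test with ties, or a proportional-odds model reporting a common odds ratio with 95% CI, replaces chi-square or Fisher.
3. Keep the efficacy rate as a descriptive figure.

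This takes one or two sentences and needs no new data, visits or patients. The price is less power than the rate would have if the benefit occurs only at the 30% threshold.

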####  AR

3.4.4

Participants will receive 8 telephone interviews (weeks 1 to 8) and will be asked the following questions: “Have you had adequate relief from your IBS pain and discomfort in the past week?” Participants simply need to answer “yes” or “no”. Respondents are defined as having answered “yes” at least 4 of the 8 weeks. AR will be evaluated at week 8.

#### Irritable Bowel Syndrome-Quality of Life Questionnaire (IBS-QOL)

3.4.5

IBS-QOL which reflects a combination of physical and mental health across eight dimensions, will be assessed at baseline, week 2, week 4 and week 8.

#### Mechanistic outcome

3.4.6

We will analyze the single-cell sequencing profiling of the T lymphocytes in peripheral blood from the TXACD granule group (n = 8) at baseline and week 4, and healthy subjects (n = 4) at baseline. In IBS-D, a complete set of transcriptional deviations enables us to search for potential molecular mechanisms and specific diagnostic biomarkers. At the same time, the therapeutic targets and pathways of TXACD in IBS-D were clarified. On the Illumina HiSeq 2000 platform, the preparation and deep sequencing of the transcriptome libraries will be performed by Shanghai OE Biotech Co., Ltd (Shanghai, China).

### Safety assessment

3.5

Participants will undergo laboratory tests at baseline and week 4, including liver and kidney function (ALT, AST, Scr, BUN), blood routine test, urine routine test, and fecal occult blood tests. Other tests include an electrocardiograph examination.

Adverse events (AEs) will be defined in the whole trial process by TXACD granule, TXACD granule placebo, PBT or PBT placebo caused by any unpredictable and unexpected harmful effects. A research assistant will record the detailed information including symptoms, signs, severity, start date, duration, lab results, intervention, and the results of adverse events at every visit. Once severe adverse events (SAEs) occur, the event must be reported to the principal investigator, the hospital ethics Committee and the Beijing Food and Drug Administration within 24 hours, and the participants’ safety should be the top priority. The principal investigator has the power to terminate the trial if necessary.

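### The adverse event definition in section 3.5 admits only unexpected effects caused by a study product, so incidence is understated and the between-arm safety comparison can be distorted

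*Protocol article*

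**What the plan says.** Section 3.5 (Safety assessment) holds the only definition of an adverse event. It covers the trial from start to finish and concerns "TXACD granule, TXACD granule placebo, PBT or PBT placebo caused by any unpredictable and unexpected harmful effects". The recording rule follows directly and applies to each visit: "A research assistant will record the detailed information including symptoms, signs, severity, start date, duration, lab results, intervention, and the results of adverse events". No section describes a later step in which causality or expectedness is graded, and there is no separate category for adverse reactions.

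On the gravest events, section 3.5 says "Once severe adverse events (SAEs) occur, the event must be reported to the principal investigator", the ethics committee and the regulator within 24 hours. Section 2.3.4 lists as a ground for termination or withdrawal: "Serious adverse events occurred in the course of the study". Neither term is defined.

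Some safety information is collected whatever its cause. Section 3.5 says "Participants will undergo laboratory tests at baseline and week 4, including liver and kidney function", with blood, urine and stool tests, and it adds an ECG. Section 3.2 requires worsening IBS-D symptoms to be entered in the case report form and has patients keep a daily diary that includes accompanying treatments. Section 2.5 has staff record why participants withdraw.

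The Introduction names safety alongside efficacy in the primary aim. The primary outcome in section 3.4.1 is IBS-SSS response.

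**The concern.** Causality and expectedness are judgments to be made about an event after it is on record. Here they decide whether it goes on record at all. An event that the assessor considers unrelated, or already known for one of the products, falls outside the definition and so outside the recording rule. It leaves no adverse event record to reclassify, and a statistical analysis plan cannot restore events that were never collected.

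What is at stake is the safety half of the stated aim. The reported rates would be rates of suspected unexpected reactions under the name of adverse event rates. Any comparison of arms would depend on which kinds of event passed the filter.

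A smaller wording point lies beside it. Severity describes intensity and seriousness describes outcome. Section 3.5 uses severe for the events that trigger 24-hour reporting and also lists severity as a recorded attribute, while section 2.3.4 uses serious. With no definition of either, it is unclear whether the two sections mean the same events. Read as a subset of adverse events, these events would also inherit the two conditions.

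**Working it through.** The protocol gives no adverse event rate, so there is no figure of its own to reproduce. The check is first one of reading, then of arithmetic under assumed rates.

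**Reading.**

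1. Definition (3.5): a study product must be the cause, and the harm must be unexpected. "caused by any unpredictable and unexpected harmful effects" carries the second condition; naming the four products carries the first.
2. Recording (3.5): applies to adverse events, that is, to events that already meet step 1.
3. Elsewhere: no section says that all untoward occurrences are recorded. Laboratory tests, ECG, worsening IBS-D symptoms and withdrawal reasons are separate routes. They do not widen the definition, and they would not reliably catch an ordinary symptomatic reaction in a patient who stays on treatment.

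**Incidence.** Let p be the true proportion of patients with an event and c the share of those patients whose event passes the definition. The recorded proportion is r = p × c. Whenever c < 1, r < p.

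**Comparison.** The recorded difference is d = p(T)c(T) − p(P)c(P), with T for TXACD and P for pinaverium. All values of p and c below are assumptions.

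| True T v P | Captured T v P | Recorded T v P | Recorded difference | True difference |
|---|---|---|---|---|
| 15% v 30% | 50% v 50% | 7.5% v 15% | −7.5 points | −15 points |
| 15% v 30% | 90% v 50% | 13.5% v 15% | −1.5 points | −15 points |
| 15% v 30% | 50% v 90% | 7.5% v 27% | −19.5 points | −15 points |
| 20% v 20% | 50% v 50% | 10% v 10% | 0 | 0 |
| 20% v 20% | 90% v 50% | 18% v 10% | +8 points | 0 |
| 20% v 20% | 50% v 90% | 10% v 18% | −8 points | 0 |

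With 72 patients randomised 1:1 there are 36 per arm. In the fifth row, 0.20 × 36 = 7.2 patients per arm truly have an event, while 0.18 × 36 = 6.5 and 0.10 × 36 = 3.6 are recorded.

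**Can capture differ by arm in a blinded trial?** Section 2.4 blinds doctors and patients, so the filter sees the type of event and not the arm. Suppose each affected patient has one type of event. Let f(k) be the share of events of type k that pass, the same in both arms, and w(k) the share of an arm's affected patients with type k. Then c for that arm is the sum of w(k) × f(k). If both arms have the same mix of event types, c is equal: the risk ratio is preserved (7.5/15 = 15/30 = 0.5) and the difference shrinks by the factor c. If the mixes differ, c differs even under perfect blinding. The documents list no reactions for either product, so the mixes, and hence the sign and size of the effect, cannot be worked out.

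**The case against.** The best defence has four parts.

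- **Translation.** The sentence is visibly broken. It names both placebos as sources of harm and covers the whole trial, so the intended meaning may be closer to any harm arising under study treatment. This stands as a possibility, and it means literal application is plausible rather than certain. But no other section corrects the wording. Nor is this detail that an article leaves to a fuller document: a definition is given, and it is the wrong one.
- **Other routes.** A reader might infer that known or unattributed events vanish altogether. The documents do not support that. Laboratory and ECG abnormalities, worsening IBS-D symptoms and reasons for withdrawal are collected regardless of attribution. The loss is partial.
- **Blinding.** A reader might infer that the filter favours one arm, with pinaverium's familiar reactions dropping out as expected while those of TXACD remain. The documents do not support that either. They list no known reactions for either product. The Discussion cites an earlier clinical trial of TXACD, so it is not undocumented. The double-blind, double-dummy design makes the filter act on event type. What remains is that the comparison can be distorted, not that it is distorted in a known direction.
- **Reach.** The primary outcome is a symptom response, which this definition does not touch. That is correct; the point concerns safety only.

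On severe versus serious, loose wording is the simplest explanation, since section 3.5 attaches the abbreviation SAEs. A missed report is possible but is not shown.

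**Conclusion.** The definition in section 3.5 is badly fixed and should be corrected. If it is applied as written and some events fail either condition, adverse event incidence is understated; this needs no assumption about rates. The between-arm comparison can also be distorted. Under the assumed rates above the recorded difference ranges from half the true one, through near disappearance (−1.5 against −15 points), to an exaggeration (−19.5 points), and with equal true rates it reaches 8 points in either direction. These figures show only that distortion is possible in either direction and can be material. They are not estimates for this trial, because the documents give neither event rates nor known reactions. The conclusion rests on staff following the text literally and on no fuller instruction overriding it. The mismatch between severe and serious is a secondary wording point.

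**What to change.** 1. In section 3.5, define an adverse event as any untoward medical occurrence during the whole trial, from consent, whether or not it is considered related to a study product or expected. Identify events after the first dose as such. Starting the definition at the first dose would narrow the present window, which includes the run-in.
2. Record causality and expectedness as separate assessments, made under blind.
3. Report all-cause events and related events by arm, in separate tables.
4. Reconcile the severe events of section 3.5 with the serious events of section 2.3.4 by using one term, defined by outcome, and keep severity as a grade of intensity. What follows clinically from such an event remains for the sponsor to state.

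The cost is a change of wording in the protocol and case report form, and slightly more events to record at visits that already take place. The change is best made early, because events not recorded during the trial cannot reliably be recovered afterwards.
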